## Abstract

**Background:**

Focal brain lesions following a stroke of the middle cerebral artery induce large-scale network disarray with a potential to impact multiple cognitive and behavioral domains. Over the last 20 years, non-invasive brain neuromodulation via electrical (tCS) stimulation has shown promise to modulate motor deficits and contribute to recovery. However, weak, inconsistent, or at times heterogeneous outcomes using these techniques have also highlighted the need for novel strategies and the assessment of their efficacy in ad hoc controlled clinical trials.

**Methods:**

We here present a double-blind, sham-controlled, single-center, randomized pilot clinical trial involving participants having suffered a unilateral middle cerebral artery (MCA) stroke resulting in motor paralysis of the contralateral upper limb. Patients will undergo a 10-day regime (5 days a week for 2 consecutive weeks) of a newly designed high-definition transcranial direct current stimulation (HD-tDCS) protocol. Clinical evaluations (e.g., Fugl Meyer, NIHSS), computer-based cognitive assessments (visuo-motor adaptation and AX-CPT attention tasks), and electroencephalography (resting-state and task-evoked EEG) will be carried out at 3 time points: (I) Baseline, (II) Post-tDCS, and (III) Follow-up. The study consists of a four-arm trial comparing the impact on motor recovery of three active anodal tDCS conditions: ipsilesional DLPFC tDCS, contralesional cerebellar tDCS or combined DLPFC + contralesional cerebellar tDCS, and a sham tDCS intervention. The Fugl-Meyer Assessment for the upper extremity (FMA-UE) is selected as the primary outcome measure to quantify motor recovery. In every stimulation session, participants will receive 20 min of high-density tDCS stimulation (HD-tDCS) (up to 0.63 mA/$${\mathrm{cm}}^{2}$$) with $${\mathrm{\pi cm}}^{2}$$ electrodes. Electrode scalp positioning relative to the cortical surface (anodes and cathodes) and intensities are based on a biophysical optimization model of current distribution ensuring a 0.25 V/m impact at each of the chosen targets.

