### Inclusion criteria

 The following inclusion criteria have been established as to be fulfilled by potential participants: (1) to have received a diagnosis of supratentorial ischemic or hemorrhagic unilateral stroke supplied by the middle cerebral artery (i.e., encompassing frontal–temporal-parietal regions); (2) to be enrolled in a “live” rehabilitation program in the Rehabilitation and Physical Medicine department of our institution; (3) to be between 18 and 85 years old; (4) to have suffered a stroke within 4 and 12 months prior to enrollment; (5) to have signed the informed consent form.

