### Non-inclusion criteria

Stroke participants presenting at least one of the following criteria will not be able to participate in our study: (1) unstable medical condition (e.g., affected by infections, with assisted ventilation, having suffered or actively suffering epilepsy or recurrent seizures, untreated psychiatric disorders, or being under an active treatment with sedative drugs); (2) participants presenting contraindications to tDCS according to the most current international NIBS safety guidelines [10]; (3) participants presenting cognitive impairments-such as severe aphasia or neuropsychiatric deficits-limiting their comprehension and their ability to follow instructions. The verification of non-inclusion criteria will be documented by means of an in-house screening questionnaire.

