### Outcome measures

In agreement with our objectives, the primary outcome measure (addressing the main and key objective) of our trial will evaluate changes in the Fulg-Meyer Assessment (FMA) for the impaired upper limb. A set of secondary outcome measures recorded prior to and following tDCS treatment (addressing study objectives 2, 3, and 4) will assess respectively: (2.1) Patient’s performance in a series of computer-based behavioral tasks evaluating visuo-motor adaptation (anterior cerebellar lobe contributions) and also sustained attention and cognitive control (prefrontal contributions); (2.2) Changes in resting-state and task-evoked EEG recordings and (2.3) set of clinical scales evaluating global stroke severity, cognitive impairment and their recovery, and correlations with predicted electric field distribution model features and stroke lesion hallmarks revealed by structural MRI neuroimaging. Find below a detailed explanation of the different outcome measures employed in our study.

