#### Fugl-Meyer Assessment (FMA)

Addressing the primary or key goal of our study, the Fugl-Meyer Assessment (FMA) will be used to evaluate upper limb motor improvements. This is a widely employed tool used to assess motor impairment in post-stroke participants and considered one of the most comprehensive and reliable quantitative measures for motor hemiplegic dysfunction [46]. Among the sub-sections of this assessment we will focus on evaluating the upper limb/extremity motor domain (FMA-UE). Even so, the lower limb/extremity section of the assessment (FMA-LE) will be also administrated to evaluate the status and changes in lower limb motor function. The FMA-UE and FMA-LE include a series of items measuring movement, coordination and reflexes, each one scored on a 3-point ordinal scale (0 = cannot perform, 1 = performs partially, 2 = performs fully), with a total score of 0 points equaling absolute hemiplegia, and 100 points signalling sound motor function; of these 100 points, 66 are attributed to the upper extremity (FMA-UE) and 34 to the lower extremity (FMA-LE). For intra-subject pre-post-intervention assessments, an improvement greater than 6 points is usually defined as clinically significant.

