#### Visuo-motor adaptation task

A visuo-motor adaptation task known to assess contributions from the anterior cerebellar lobe to voluntary motor function [47–50] programmed in a MATLAB environment (R2019a, Mathworks, USA) and Psycho-Toolbox will be implemented. During the task, participants will seat in a comfortable chair in an isolated room with no distractions at a distance of 57 cm (arm’s reach) in front of a 15-inch computer monitor, holding a hand-joystick with their impaired paretic upper limb. Hand splints to ensure correct attachment to the joystick will be employed if necessary for all subsequent measures to keep conditions constant. During the task, the joystick position will be displayed as a red dot of 1-cm diameter. Participants will be asked to complete a series of consecutive trials to direct the cursor (a red dot) from the center of the screen (starting point) towards the interior of a randomly allocated peripheral target displayed as a green circle. Each trial will start with the green circle and the red dot in the center of the screen. Subsequently, additional green circles (targets) will appear randomly in 4 possible locations, equally spaced around a virtual circle respecting a homogeneous 5 cm distance from the starting point. Participants will have 10 secs to move the red dot and place it inside the circle and maintain such position for 0.5 s. Once completed, the green circle will jump back to the starting point, and  participants had to replace the dot in the starting position to complete the trial. During the inter-trial interval (1.5 secs), a full gray screen with a center stimulus (“ + ”) will be displayed to keep participants alert and ready for a subsequent trial. If the trial is not successfully completed, hence the participant does not succeed in placing the dot inside the circle during the allotted time window, the circle will automatically jump to the starting point. Visual feedback of the dot and the circles will be displayed in real time (see Fig. 4A). The task will be divided into 2 consecutive blocks. The first block (familiarization) will consist of 32 trials, and will be followed by a second block (motor adaptation)including 64 trials. During the familiarization block, trials will be conducted as previously described. During the motor adaptation block, a “force-field-like” perturbation will be implemented by introducing a constant 45° angular rotation between the trajectory of the red dot trajectory and the real movement of the joystick, deviating the trajectory of the former and forcing participants to compensate for such shifts in order to reach the target in the alloted time, hence engaging visuo-motor adaptation (learning) skills.

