## Data analyses

### Analysis of clinical and cognitive performance outcome measures

Outcomes extracted from computer-based tasks and clinical scores (see the previous section) will be analyzed to explore the differential ability of active tDCS conditions compared to sham stimulation to induce upper limb motor recovery following a stroke. For the clinical tests (FMA, NIHSS, MoCA, and hemispatial neglect tests), mean group scores post vs. pre-tDCS baseline intervention,and during the follow-up assessment, will be compared across experimental groups. Sociodemographic data will also be compared between treatment groups (Group 1: ipsi-DLPFC, Group 2: contra-CEREB, Group 3: ipsi-DLPFC + contra-CEREB, Group 4: SHAM) to identify potential collapse factors.

In order to quantify changes in motor performance with the visuo-motor adaptation task,and assess tDCS effects applied over the cerebellum or the dorsolateral prefrontal areas on upper limb voluntary motion, the following set of measures will be used: (i) the angular trajectory error (“SumErr”; cm) estimating accuracy, consisting of the sum of observed deviations from the ideal linear trajectory at peak tangential velocity (PV)for each trial of the motor adaptation block; (ii) the area under the learning curve (AUC) measuring patients’ adaptation rate,calculated by performing a power fit on the mean learning values of each participant; (iii) the coefficient of variation (CV)measuring the variability of motor performance during the adaptation plateau phase (i.e., when the AUC is stabilized and reaches stable levels) and calculated as the standard deviation (SD) divided by the mean over trials belonging to the plateau phase (AUC/Time-to-target). All these metrics will be represented in ordinal and mean group scores for post vs. pre-tDCS baseline intervention, and for the follow-up milestone and compared across tDCS groups.

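### The visuo-motor outcome needs movement of the paretic arm, but entry sets no minimum and the analysis-set rules conflict, so who contributes an adaptation score can depend on recovery

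*Protocol article*

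**What the plan says.** **Who enters.** The abstract speaks of participants "having suffered a unilateral middle cerebral artery (MCA) stroke resulting in motor paralysis of the contralateral upper limb". The Inclusion criteria begin with "to have received a diagnosis of supratentorial ischemic or hemorrhagic unilateral stroke supplied by the middle cerebral artery" and add enrolment in rehabilitation, age, time since stroke and consent. The Non-inclusion criteria screen out cognitive deficits "limiting their comprehension and their ability to follow instructions". Neither list mentions arm movement. The arm section of the Fugl-Meyer scale runs from 0 to 66, "with a total score of 0 points equaling absolute hemiplegia", and no part of that range is excluded.

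**What is measured.** The Outcome measures section pairs each stimulation target with a computer task, and the cerebellar one is "visuo-motor adaptation (anterior cerebellar lobe contributions". The Visuo-motor adaptation task section has patients work a joystick with the impaired arm, with a splint if needed to keep the hand attached. There are 32 familiarisation and 64 perturbed trials, and the target lies 5 cm from the start on screen. "Participants will have 10 secs to move the red dot and place it inside the circle and maintain such position for 0.5 s". The prefrontal task (AX-CPT) uses the unimpaired hand.

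**How it is scored.** The section on analysis of clinical and cognitive outcomes takes trajectory error at peak velocity for each perturbed trial. It takes an area under the learning curve "calculated by performing a power fit on the mean learning values of each participant", and a coefficient of variation over the plateau. Group means are then compared.

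**Who is analysed.** The last paragraph of Statistical analyses invokes intention to treat. It then says that patients with data at W0, W3 and W7 are analysed, that all data on hand are used, and that gaps are filled through a constrained longitudinal data analysis (cLDA).

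**The concern.** A patient who cannot reach has no velocity peak, no learning curve and no plateau. For that patient adaptation is undefined, which is different from a value that exists but was not recorded. Whether a patient can be scored therefore depends on arm function, which is what the primary outcome measures and what the treatment is meant to change. If the analysis lets in patients once they can move, the arms are compared on sets chosen partly by the result of treatment.

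At stake is the secondary objective on motor adaptation, together with the Discussion's plan to use the two tasks to verify that motor gains are mediated by the stimulated networks. The problem is one-sided: the cerebellar task is limited by paresis and the prefrontal task is not.

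**Working it through.** **1. Can a non-mover be randomised?** Yes. There are five inclusion and three non-inclusion criteria, and none concerns movement. An arm score of 0 is admissible.

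**2. What do the metrics need?** Error at peak velocity needs a movement but not arrival at the target. The fitted curve needs a sequence of movements. The plateau measure needs a curve that stabilises. With no reach, none carries adaptation meaning. With weak reach, the first can still be computed but reflects weakness as well as adaptation. The splint helps grip, not reach.

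**3. What do the analysis rules do with each patient?**

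| Arm movement | Three-visit rule | All data plus cLDA imputation |
|---|---|---|
| None at W0, none later | not analysed | given an imputed score, or none |
| None at W0, some at W3 | not analysed if there is no W0 score | enters because of recovery |
| Some at W0, lost later | dropped on a later result | W0 kept, later score imputed |
| Severe paresis throughout | analysed, weakness mixed in | the same |

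The article also does not settle whether a block of 64 failed trials counts as data. If it does, a meaningless value is averaged under either rule.

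**4. How large could the selection bias be?** The article gives no input, so everything here is assumed:
- Baseline motor ability M0 is standard normal.
- Adaptation is A = ρ·M0 + √(1−ρ²)·e, untouched by treatment, with ρ = 0.3 to 0.7.
- Later ability is M1 = M0 + g + 0.5·e′, with g = 0 in sham and 0.5 in an active arm.
- A patient is measurable when ability exceeds the f-th quantile of M0, with f = 10% to 40%.
- There is one post-treatment visit and 2,000,000 simulated patients per arm.

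The table gives the spurious active-minus-sham difference in mean A, in SD, over the range of ρ.

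| f | Measurable later, sham / active | All available data | Complete cases |
|---|---|---|---|
| 10% | 87% / 94% | −0.032 to −0.074 | −0.015 to −0.036 |
| 20% | 77% / 88% | −0.045 to −0.105 | −0.019 to −0.043 |
| 30% | 68% / 82% | −0.056 to −0.128 | −0.021 to −0.046 |
| 40% | 59% / 75% | −0.064 to −0.149 | −0.021 to −0.050 |

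The bias runs against the active arm under both rules and is larger when all available data are used.

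**5. How many patients remain?** The article states 15 per arm (4 × 15 = 60) with no effect size or power, so there is no power figure to reproduce. For a two-sample t-test at two-sided 5% and an assumed difference d = 1 SD, df = 2n − 2 and the noncentrality is d·√(n/2).
- n = 15: √7.5 = 2.74, power 0.75
- n = 12 (20% unmeasurable): √6 = 2.45, power 0.65
- n = 9 (40% unmeasurable): √4.5 = 2.12, power 0.51

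**The case against.** The strongest reply is that the article already contains a rule that closes the main route. It compares post-treatment with baseline scores and says that patients with data at all three visits are analysed. A patient with no baseline score then cannot appear at W3. This is right as far as it goes, but the same paragraph also admits all available data and imputes the rest, and nothing says which sentence governs.

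Other points stand in part:
- **Severe patients.** A reader might infer that they give no valid score. That is firm only for absent movement. Error at peak velocity does not need target arrival, and the joystick excursion behind 5 cm on screen is not stated. The article also calls the arm paretic, so paralysis is used loosely.
- **Feasibility.** Trial status reports a pilot of 8 that tested some of the tasks, and 11 participants who completed the protocol. This bears on how many patients cannot do the task, but it does not show that all can.
- **Other cerebellar information.** EEG is recorded during the task, including at PO9 and PO10, and individual field strength at the target is related to outcomes. The joystick task is the only behavioural readout, not the only readout of any kind.
- **Disclosure.** The Discussion concedes that severity may limit task performance. Its answer is minimisation on sex, age and stroke type. That list omits severity and cannot make a non-mover measurable.
- **Analysis plan not shown.** Scoring of failed trials may well be set there, and its absence here is no fault. The conflict between the analysis-set sentences is on the page.

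**Conclusion.** The point holds for one secondary outcome and the mediation argument built on it. As written, the plan may score or impute adaptation where it is undefined, or admit patients because they recovered. The likely bias is small, about 0.02 to 0.15 SD, and rests wholly on the assumed share unmeasurable, motor gain and correlation. With 12 per arm the standard error of a difference is √(2/12) = 0.41 SD, so even the upper end is about 0.15/0.41 = 0.37 of a standard error.

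A reader might infer that a real benefit would show up as harm. For example, 10 patients measurable at baseline, joined at W3 by 2 whose error is 1 SD worse, would shift the arm mean by 2/12 = 0.17 SD. That example invents its inputs and allows no recovery under sham, whereas the article expects spontaneous recovery and rehabilitation effects. The documents do not support so strong a claim. Nor do they give a share of patients unable to reach, so the power figures are illustrations only. FMA-UE can be scored at any severity, and the primary comparison is untouched by this measurement problem.

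**What to change.** Leave entry as it is. In the outcome-analysis and Statistical analyses sections, for the visuo-motor outcomes only:

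1. Define the analysis set from W0 alone, by a prespecified minimum number of the 32 unperturbed familiarisation trials completed. Half (16) is one workable cut-off; add a sensitivity analysis at another, since trial completion also requires the 0.5 s hold.
2. Use the same patients at W3 and W7, and impute no adaptation score for anyone outside the set.
3. Report the number outside the set by arm.
4. State that the three-visit sentence removes nobody from the FMA-UE analysis, where all randomised patients stay.

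Membership then depends only on pre-treatment data, so the randomised comparison is kept within the set. The cost is one rule using trials already in the task, which can be fixed before unblinding. The downsides are that the adaptation result applies only to patients with some arm movement at baseline, and that the power lost from fewer evaluable patients is not recovered.

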**Discussion:**

Our trial will gauge the therapeutic potential of accumulative sessions of HD-tDCS to improve upper limb motor and cognitive dysfunctions presented by middle cerebral artery stroke patients. In parallel, we aim at characterizing changes in electroencephalographic (EEG) activity as biomarkers of clinical effects and at identifying potential interactions between tDCS impact and motor performance outcomes. Our work will enrich our mechanistic understanding on prefrontal and cerebellar contributions to motor function and its rehabilitation following brain damage.

**Trial registration:**

ClinicalTrials.gov NCT05329818. April 15, 2022.

**Supplementary Information:**

The online version contains supplementary material available at 10.1186/s13063-023-07680-8.

## Introduction

Middle cerebral artery (MCA) strokes are known to cause direct structural damage to key sensory-motor networks in charge of executing and controlling voluntary motion actions in frontal and anterior parietal cortical or in associated subcortical structures. Despite the influence of lesion location and extent [1–3], the magnitude of motor performance deficits following stroke [4–6] cannot be solely explained by ischemic damage on motor systems but also by diaschetic effects altering network interactions with local and distant structures contributing substantially to optimal motor activity.

Transcranial direct current stimulation (tDCS) is among the most popular non-invasive brain stimulation approaches currently used in clinical settings. It is characterized by its portability, low cost, ease of use, a safe profile of side effects, and high flexibility to target several locations simultaneously. Transcranial DCS is based on the application of a low-intensity continuous current inducing polarity-dependent sub-threshold shifts of neuronal resting membrane potential towards (anodal) or away (cathodal) from the firing threshold [7–10].

By virtue of such effects, whereas single sessions of tDCS have shown the ability to transiently modulate corticospinal excitability, periodical sessions of such simulation promote long-term potentiation/depression-like plasticity [11]. Transcranial DCS has been used as a therapeutic intervention to boost cognitive and motor recovery following stroke in diverse settings and evaluated with regards to its ability to improve voluntary upper limb function [12–16]. Despite its success in small samples of selected participants, the effects reported by accumulative tDCS interventions in stroke have often been shown to be inconsistent when applied to larger cohorts of patients [17]. Additionally, tDCS outcomes have been found to be highly influenced by variables such as post-stroke-to-treatment-onset time-lag, lesion site and volume, a large variety of stimulation parameters (electrode location, current intensity, density, regime periodicity, etc.), and interindividual head and brain anatomical differences affecting the distribution of tDCS-generated electric fields [18, 19].

Over the last decade, classical non-invasive brain stimulation (NIBS) approaches with transcranial magnetic stimulation (TMS) or with tDCS have privileged clinical strategies based on either the upregulation of directly affected primary motor systems or the downregulation of homologue motor networks of the spared contralesional hemisphere linked with the former via inhibitory trans-callosal inter-hemispheric projections.

Nevertheless, the neural signature of MCA lesions has revealed strong interactions with alterations in sustained attention (engaging prefrontal and fronto-parietal systems) and large-scale desynchronization phenomena, both key factors limiting motor function or precluding recovery after brain damage [20–22]. More specifically, the severity of motor deficits has been associated with the strengthening of impaired inter-hemispheric functional connectivity between the dorsal attention network (DAN) and sensory-motor networks (SMN) [23–26] and high- and low-frequency oscillatory abnormalities (decreases and increases respectively) in the injured hemisphere [27, 28]. Likewise, a connectome-based predictive model exploring fractional anisotropy (FA) in stroke has highlighted the role of the ipsilesional dorsolateral prefrontal cortex (DLPFC) and cerebellar areas subtending motor symptoms and suggested their potential to convey motor recovery when manipulated with NIBS interventions [29]. In such a context conventional therapeutic neurostimulation directly modulating the excitability of damaged areas in charge of mapping lost functions has shown inconsistent outcomes. Heneforth, recent innovative approaches [30, 31] have been focused on reversing abnormal large-scale network signatures by inducing synergistic effects from spared cortical regions contributing to impaired function [30, 31].

On such basis and superseding the clinical limitations of traditional approaches [32–34], we here aim at providing evidence that a multi-site tDCS stimulation approach targeting simultaneously the dorsolateral prefrontal cortex and the anterior lobe of the cerebellum will be able to drive significant clinical improvement in upper limb motor function compared to a placebo intervention, and also that such effects would be greater than the isolated stimulation of either site individually. Importantly, a battery of secondary measures relying on cognitive tasks assessing cerebellar and prefrontal contributions to motor function, sustained and selective attentional processes, EEG recordings and structural MRI neuroimaging will inform on some of the neural mechanisms involved in such recovery.

